##### **9.1.4.Comparison of the variation in performance scores between groups 1 and 2 = Evaluation of the effect of repeated simulation on performance**

To study variation in performance (global performance, IO access and teamwork evaluation scores) between the time point of inclusion (T0) and the simulation program's endpoint, the relative variation of various scores will be calculated  $\{([final\ score] - [score\ T0]) / (score\ T0)\}$ . These relative variations will be compared between the 2 groups using a Student's t-test. An ANOVA test will be used to search for a possible effect due to participant status.

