#### 4.2. Secondary outcome measures

##### 4.2.1. Evaluation of performance

**Team performance** of a simulated infant shock management will be assessed by three ways:

- **Global team clinical performance** will be evaluated using performance assessment scale ("TAPAS"), designed by the Simulation Laboratory and in validating process (Oriot 2013, unpublished data).
- **IO access procedure process and success** of the insertion technique: evaluated by
  - An assessment scale - IOPAS - *Intraosseous Performance Assessment Scale* (Oriot 2012),
  - Time to decision,
  - And duration of procedure (Oriot 2012) (cf. Appendix).
- **Teamwork performance** will be evaluated using the following validated scales:
  - concerning **Leadership assessment**: BAT – *Behavioural Assessment Tool* (Anderson 2010) (cf. Appendix)
  - concerning **Global Teamwork assessment**: CTS - *Clinical Teamwork Scale*, CTS (Guise 2008) (cf. Appendix)

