#### **4.2.2.Evaluation of the effect of repeated simulation sessions on stress and performance**

Effect of repeated simulation sessions on stress and performance will be assessed by the same stress parameters and team performance scores.

To study evolution of stress, we shall calculate the relative variation of different variables obtained from performance scores. Relative variation will be defined by the following calculation:  $([\text{final score}] - [\text{score T0}]) / (\text{score T0})$

We shall study the effect of repeated simulation on the parameters of stress. Finally, the senior physician's stress management strategies will be deduced from previous evaluations and evaluated according to 2 different manners, inspired by the axes proposed by Wetzel (Wetzel 2010):

- Observation during simulation
- Video recording viewing by the supervisors

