#### **4.3.4.Supervisors and evaluation**

Two independent supervisors at a time will evaluate each simulation session of the Sim-Stress research protocol.

These supervisors, who are members of the University Hospital of Poitiers

(CHU de Poitiers) Simulation Laboratory, will be chosen in random manner. They each have different specialities, and are all simulation trainers, qualified in performing debriefing sessions.

This team of supervisors will consist of [name] (pediatric intensivist), [name] (pediatric emergency physician), [name] (surgical intensivist), [name] (adult emergency physician), and 4 emergency or pediatric fellows. They will analyze global performance with the respect to algorithm, IO access performance and global teamwork - leadership and communication. The mean between the two supervisors' scores will be used as the reference value. Interobserver reproducibility will be calculated according to the scale used.

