##### 4.5.1.2. Drawing lots for random distribution of each team into one of the 2 of simulation session programs

Once the teams have been constituted, drawing lots will be performed according to a list that will be previously established by the study's methodologist, so as to distribute the 12 teams in 2 groups of 6 teams :

**Group 1** will be constituted by 6 teams of 4 persons each, and each of these teams will undergo simulation sessions once every **6 weeks**, for a total of 9 sessions in 12 months.

**Group 2** will be constituted by 6 teams of 4 persons each, and each of these teams will undergo simulation sessions once every **6 months**, for a total of 3 sessions in 12 months.

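### Section 9.1.4 tests the repetition effect on performance by relative change from T0, which is inefficient with 6 against 6 teams if the effect is additive, and adds a status ANOVA that team-level scores cannot support

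*Protocol*

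**What the plan says.** Section 9.1.4 covers global performance, IO access and teamwork. Between inclusion (T0) and the end of the programme, "the relative variation of various scores will be calculated" as (final − T0)/T0. The test follows: "These relative variations will be compared between the 2 groups using a Student's t-test". The section states no adjustment for T0 and no rank-based alternative, although 9.1.2, 9.1.3 and 9.1.5 each name one. It then adds: "An ANOVA test will be used to search for a possible effect due to participant status".

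Section 4.5.1.2 sets the size of the comparison, since the draw will "distribute the 12 teams in 2 groups of 6 teams". Section 4.2.1 lists the global scale, the IO access scale and times, BAT and CTS together as team performance, which "of a simulated infant shock management will be assessed by three ways". Section 4.3.4 reduces each to one number per session: "The mean between the two supervisors' scores will be used as the reference value".

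Section 4.2.2 gives the same formula as 9.1.4 under another purpose: "To study evolution of stress, we shall calculate the relative variation of different variables obtained from performance scores". Section 9.1.3 mentions linear mixed models over all sessions, but only as a possibility.

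**The concern.** A ratio to baseline places the error of the T0 score in both numerator and denominator. A team with a poor first session then carries more weight, the distribution is skewed, and a chance difference in T0 between two groups of six teams passes into the outcome. IOPAS, BAT and CTS all start at 0, so the ratio is undefined at the bottom of the scale and erratic near it. The protocol already collects T0, and using it as a covariate would avoid these features.

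The status ANOVA needs values that differ between members of a team. If the team is scored as a unit, there is nothing for status to explain.

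This is the only randomised between-group comparison of performance that the plan commits to. Section 9.2 plans no power for it and leaves power for secondary questions to a calculation after the data are in. Efficiency that can be had by a change of wording is therefore worth having.

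**Working it through.** **Figure in the plan.** There is none to reproduce for this comparison. The 48 participants in 9.2 are sized for a correlation of 0.50 between stress and performance.

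**Inputs from the protocol.** 6 against 6 teams (4.5.1.2); 5% significance level (9.3), taken as two-sided; SD of the IO access score 1.02 on a 20-point scale (9.2).

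**Inputs assumed.** The protocol does not give them, so ranges are shown:
- Group effect 1.5 SD, additive in scale points.
- T0–final correlation ρ of 0.3, 0.5 or 0.7.
- Common gain in both groups of 15% of the T0 mean.
- CV of T0 of 8.5%, 15% or 30%. The first comes from the SD of 1.02 and an assumed T0 mean of 12: 1.02/12 = 0.085.

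**Large-sample comparison.** Let k be the mean final score divided by the mean T0 score, with equal SDs at both times and a small CV. The variance of relative change against that of the ANCOVA residual is

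(1 + k² − 2ρk) / (1 − ρ²).

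At ρ = 0.5:
- k = 1: (1 + 1 − 1)/0.75 = 1.33.
- k = 1.15: (1 + 1.3225 − 1.15)/0.75 = 1.56.
- k = 1.5: (1 + 2.25 − 1.5)/0.75 = 2.33.

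**Simulation at 6 against 6 teams.** The t-test on (final − T0)/T0 has 10 degrees of freedom. The ANCOVA of final score on group and T0 has 9. Each setting used at least 20,000 simulated trials, and repeat runs agreed to about one percentage point.

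| CV of T0 | Relative change, ρ = 0.3 / 0.5 / 0.7 | ANCOVA, ρ = 0.3 / 0.5 / 0.7 |
|---|---|---|
| 8.5% | 43 / 55 / 75% | 64 / 71 / 86% |
| 15% | 39 / 51 / 70% | 63 / 72 / 87% |
| 30% | 30 / 39 / 54% | 64 / 72 / 86% |

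The gap also depends on the common gain. With a gain of 1 SD instead of 15%, CV 30% and ρ = 0.5, power is 33% against 72%.

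**Type I error.** With no group effect, relative change rejects in about 5% of trials at CV 8.5% and 15%, and in about 4% at CV 30%. ANCOVA rejects in about 5% throughout.

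**Counter-check.** If each team's gain is strictly proportional to its T0 score, the ranking reverses: about 64% for relative change against about 58% for ANCOVA.

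**Status ANOVA.** Sections 4.2.1 and 4.3.4 give one value per team and session, and every team contains all four roles. If that value is copied to the four members, each role has the same 12 numbers. The between-role sum of squares is then 0, so F = 0 and p = 1 whatever the data.

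**Section 4.2.2 beside 9.1.4.** The formula is identical and both sections apply it to performance scores. Section 9.1.4 introduces it as a study of performance, 4.2.2 as a study of stress. Section 4.2.2 then turns separately to the stress parameters.

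**The case against.** **The power gap depends on an additive effect.** This stands, and the conclusion carries that condition. Strict proportionality is hard to sustain on bounded scales with a ceiling, but the protocol neither states nor excludes it.

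**A reader might infer that the planned test is invalid or gives false positives.** The simulations do not support this. Type I error is about 4–5% over the CV range in the table and drifts lower, not higher, when T0 is more variable.

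**A reader might infer that the choice of metric decides whether a realistic effect can be found.** The protocol gives no basis for calling 1.5 SD realistic. At 1.0 SD and CV 15%, power is about 21–41% for relative change against 34–54% for ANCOVA over the same correlations. Both are low, mainly because there are only 12 teams.

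**Division by zero is unlikely in practice.** A zero total on IOPAS or BAT means failing every item, and 4.3.1 has the senior physicians trained and evaluated in IO access beforehand. The argument therefore rests on dependence on baseline and loss of power, not on zero scores.

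**Only 24 of the 72 team sessions are used.** First and last sessions of 12 teams do make 24, but ANCOVA on T0 and final score uses the same 24. Section 9.1.3 tests all sessions within each group, so this is no argument for ANCOVA. Only a mixed model would use all sessions in a between-group comparison.

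**The status effect is zero only if team scores are copied to members, which the protocol does not say.** Correct. The exact statement is that no member-level score is described, so the test has no defined input. For the same reason the documents do not support inferring that the group t-test would be run on 48 copied rows; that would raise its type I error to about 37%, but the plan does not propose it.

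**A reader might infer from 4.2.2 that stress change is wrongly derived from performance scores.** The match with 9.1.4 makes a slip of wording far more likely.

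**Conclusion.** The point holds as one of efficiency and definition in a secondary analysis. Under an additive effect of 1.5 SD, relative change gives up about 11 to 21 percentage points of power at CV 8.5% (86 − 75 and 64 − 43) and about 32 to 34 at CV 30% (86 − 54 and 64 − 30). These sizes rest on the assumed effect, correlation, common gain and CV. The only dispersion figure in the protocol, with an assumed T0 mean of 12, points to the lower CV for the IO score. If gains were strictly proportional to T0, relative change would be ahead by about 6 points.

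The defect in the status ANOVA needs no assumption about effect size or dispersion. With only team-level scores described, it can tell the reader nothing about status. The wording of 4.2.2 is an editorial inconsistency and adds no weight to the rest.

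**What to change.** In 9.1.4, replace the t-test on relative variation by an ANCOVA of the final score on group and T0 score, with the team as unit (n = 12). Report the adjusted difference in scale points with its 95% confidence interval. Relative change may remain as a description. A prespecified mixed model over all sessions is an option, provided the section fixes it in advance and names the between-group contrast to be reported.

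Delete the ANOVA by participant status for team scores.

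Reconcile the sentence in 4.2.2 with 9.1.4, since stress there appears to stand for performance.

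The cost is wording and one degree of freedom (9 instead of 10). No further data, sessions or participants are needed.

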##### **9.1.5.Comparison of stress between groups 1 and 2 = Evaluation of the effect of repeated simulation on stress**

The various stress markers (biological, electrophysiological and psychological) will be compared between the 2 groups 1 and 2 by means of a Student's t test or, if necessary, a Mann-Whitney non parametric test.

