### 4.4. Study schedule

#### 4.4.1. Time schedule of measurements

Time schedule of measurements

| Variables         |                    | day prior | Before Sim | Sim | Post Sim | Debrief | Post debrief | H+2 | 1 week | 1 month |
|-------------------|--------------------|-----------|------------|-----|----------|---------|--------------|-----|--------|---------|
| PERFORMANCE       | Global Performance |           |            | X   |          |         |              |     |        |         |
|                   | IO access          |           |            | X   |          |         |              |     |        |         |
|                   | Leadership (BAT)   |           |            | X   |          |         |              |     |        |         |
|                   | Teamwork (CTS)     |           |            | X   |          |         |              |     |        |         |
| STRESS PARAMETERS | Salivary cortisol  | X         | X          |     | X        |         | X            |     |        |         |
|                   | Holter parameters  | X         | X          | X   | X        | X       | X            | X   |        |         |
|                   | BP HR              | X         | X          |     | X        |         | X            |     |        |         |
|                   | SOM                |           | X          | X   |          |         |              |     |        |         |
|                   | STAI scale         | X         | X          |     | X        |         | X            |     |        |         |
|                   | EIS-R scale        |           |            |     |          |         |              |     | X      |         |
|                   | PCLS scale         |           |            |     |          |         |              |     |        | X       |

This plan will be repeated on each and every simulation session, that either every 6 weeks (as concerns the teams of group 1) or every 6 months (as concerns the teams of group 2).

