#### **4.4.2. Quantification of sessions and various evaluations**

##### 4.4.2.1. Number of participants included in the study

12 teams of 4 persons = **48 participants**

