##### 4.4.2.3. Number of individual simulation sessions :

Group 1: 6 teams x 4 members per team x 9 sessions = 216

Group 2: 6 teams x 4 members per team x 3 sessions = 72

TOTAL = 216 + 72 = 288 individual simulation sessions

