### **7.2. Description of the parameters involved in the evaluation of stress**

Parameters involved in the *evaluation of stress* will be estimated for every participant, and are described in paragraph 4.2.1

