##### **9.1.3.Evaluation of performance score variations**

Variations in global team, IO access, and teamwork performance scores will be estimated in terms of temporal sequence. In each of the groups 1 (9 sessions) and 2 (3 session), score modifications between the various simulation sessions will be tested by means of an ANOVA for repeated measures (or the Friedman non parametric test, if need be).

Concerning the entire study population, linear mixed effects models (for continuous responses observed over time) will eventually be used envisaged so as to take into account, in a common analysis, the entire set of data collected throughout the various sessions, and, more notably, parameters involved in the development of stress management strategies compared to stress and repeated simulations.

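### Section 9.1.5 compares participant-level stress between groups with a t or Mann-Whitney test although teams were randomised, so the 5% level is not controlled

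*Protocol*

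**What the plan says.** - **Unit of allocation.** Protocol 4.5.1.2 draws whole teams, "so as to distribute the 12 teams in 2 groups of 6 teams". Section 4.4.2.1 gives the size as "12 teams of 4 persons", so there are 24 participants per group, with one person of each professional status in every team.
- **Unit of measurement.** Section 7.2 says that the stress parameters "will be estimated for every participant". Section 4.4.1 adds: "This plan will be repeated on each and every simulation session". Section 4.4.2.3 counts the result: "Group 1: 6 teams x 4 members per team x 9 sessions = 216" and "Group 2: 6 teams x 4 members per team x 3 sessions = 72".
- **Test.** Section 9.1.5 says that the biological, electrophysiological and psychological markers "will be compared between the 2 groups 1 and 2 by means of a Student's t test", with Mann-Whitney as the alternative. It names no team term, no session or summary over sessions, and no T0 value.
- **Neighbouring text.** Section 9.1.4 uses relative change from T0, but for performance. Section 4.2.2 mentions a final-versus-T0 relative variation for the evolution of stress, yet defines it on variables taken from performance scores. Section 9.1.3 says that "linear mixed effects models (for continuous responses observed over time) will eventually be used envisaged"; it names no team effect and does not replace the test in 9.1.5.

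**The concern.** Student's t and Mann-Whitney tests both assume independent observations. Four people who go through the same scenario together, under the same senior physician and with the same alarms and interruptions, probably share part of their stress response. Section 4.3.3 shows that the stress is deliberately built into the scenario and its surroundings. Counting them as four independent units makes the comparison look as if 48 units had been allocated, when 12 were.

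The effect of repetition on stress is one of the questions for which the two groups were randomised (3.2, 4.3.7, 6.2), and 9.3 judges it at p < 0.05. If the stated test does not run at 5%, neither its p-values nor the matching confidence intervals can be taken at face value.

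**Working it through.** **Plan's own figure.** None exists for this comparison. The number 48 in 9.2 is calculated for a correlation between stress and performance, and 9.2 leaves power for the secondary objectives to be calculated afterwards. The counts do reproduce: 6 × 4 × 9 = 216, 6 × 4 × 3 = 72, total 288.

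**Inputs from the protocol.** 6 against 6 teams; 4 members per team, one per status; 5% threshold (9.3), taken as two-sided. **Assumed, because the protocol gives neither:** the share t of marker variance that lies between teams (the within-team correlation, ICC, when s = 0) and the share s that lies between professional statuses. The remaining share, 1 − t − s, is individual.

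**True against assumed variance.** Each team has one member of each status, so status differences cancel from the group contrast.
- Variance of a team mean, as it enters the contrast: t + (1 − t − s)/4.
- Variance of a mean of six teams: [t + (1 − t − s)/4]/6 = (1 + 3t − s)/24.
- The plain t test takes it to be about 1/24, because it counts team, status and individual variance all as independent noise.
- Ratio of true to assumed variance: D ≈ 1 + 3t − s.
- True two-sided level ≈ 2[1 − Φ(1.96/√D)].

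**No status variance (s = 0).**

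| ICC | D | Formula | Simulated t test | Simulated Mann-Whitney |
|---|---|---|---|---|
| 0.05 | 1.15 | 6.8% | 6.9% | 6.3% |
| 0.10 | 1.30 | 8.6% | 8.5% | 8.3% |
| 0.20 | 1.60 | 12.1% | 12.4% | 12.3% |
| 0.30 | 1.90 | 15.5% | 15.6% | 15.0% |

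**With status variance (formula; simulation agrees within about 0.4 percentage points).**

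| s | t = 0 | t = 0.05 | t = 0.10 | t = 0.20 | t = 0.30 |
|---|---|---|---|---|---|
| 0.20 | 2.8% | 4.4% | 6.2% | 9.8% | 13.3% |
| 0.30 | 1.9% | 3.4% | 5.0% | 8.6% | 12.1% |

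Break-even is D = 1, that is s = 3t. Above that line the test is conservative; below it the test is anti-conservative. The t-test simulations used 40,000 null trials per setting with fixed status effects; the Mann-Whitney column used 5,000. A t test on the 6 against 6 team means stayed at about 5% in every setting (4.8-5.2%).

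**T0.** Ignoring a baseline that correlates 0.3, 0.5 or 0.7 with the outcome left the level of a two-sample test on independent persons at 4.8%, 5.4% and 5.0%. Adjustment would multiply the residual variance by 1 − ρ² = 0.91, 0.75 and 0.51. This is a gain in precision and has no bearing on validity.

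**Detectable difference (80% power, s = 0, no T0 adjustment).** The 24 against 24 test taken at face value: 0.83 SD. With 6 team means per group the standardised detectable difference is 1.80 team-mean SDs, so in individual SDs it is 1.80 × √(t + (1 − t)/4): 0.96 at t = 0.05 and 1.24 at t = 0.30.

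**The case against.** The strongest reply is that inflation is not established. The protocol builds teams with one person per status and itself looks for heterogeneity by status (9.1.2, 9.1.4). If professions differ markedly in stress and teams do not, the plain test is conservative. This stands: the tables above show levels below 5% whenever s exceeds 3t. It does not rescue the test, because the level then depends on two unknown variance shares and equals 5% only by coincidence.

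Three stronger readings are tempting, and the protocol does not support them.
- *Leaving out T0 distorts the error rate.* Under randomisation it does not. Nor is T0 wholly absent from the plan for stress: 4.2.2 points to final against T0, although in a sentence that refers to performance scores. The fault there is misalignment between 4.2.2 and 9.1.5.
- *All sessions will be pooled, 216 rows against 72.* Section 9.1.5 neither says so nor excludes it. If rows were pooled as independent, simulated levels would be about 18% (participant variance share 0.30, no team effect) to 41% (team share 0.20 in addition). That illustrates why the session should be named; it does not measure the error of the stated plan.
- *The mixed model in 9.1.3 is confined to performance.* It sits under that heading, but its text also mentions stress and repeated simulations. It is partial mitigation at most: it is optional and names no team effect.

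It is also fair to say that 9.1.5 does not name its unit of analysis. That individuals are meant is an inference from 7.2. A t test on team means would be sound, but nothing in 9.1.5 points to one.

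**Conclusion.** The point holds. Read with 7.2, section 9.1.5 fixes a test for independent persons on data from a team-randomised comparison, and its level is not controlled at 5%. Over the ranges assumed here the level runs from about 2% (no team effect, 30% status variance) to about 16% (ICC 0.30, no status variance). It is inflated when three times the team share of variance exceeds the status share. The protocol gives neither share, so both the size and the direction of the error are conditional; that the level is uncontrolled is not.

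A reader might infer that false positives are certainly inflated or that the primary outcome is affected. Neither follows. The comparison belongs to a secondary objective. It is nevertheless a randomised comparison tested at 5%, and the correction should be made before the data are analysed.

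**What to change.** Replace the test in 9.1.5 with the following, for each marker:
- Analyse the final session with a linear mixed model. Fixed effects: group, the T0 value of the same marker, and professional status. Random intercept for team. Kenward-Roger or Satterthwaite degrees of freedom.
- Alternatively, compare the 6 against 6 team means adjusted for T0.
- If more sessions enter, add a random participant effect and compare the groups at the roughly common times: first session, about six months, final session. Six-weekly sessions counted from week 0 fall at weeks 24 and 48 (4 × 6 and 8 × 6), six-monthly ones near weeks 26 and 52, so the match is approximate.
- Align 4.2.2 with 9.1.5, so that one place says which stress quantity is compared and how T0 enters.

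The cost is analysis wording only: no new participants, sessions or measurements. The intervals will usually be wider where team variance matters. Without T0 adjustment the detectable difference is about 0.96 to 1.24 SD for ICC 0.05 to 0.30, against a nominal 0.83 SD for a test that does not hold its level. Adjusting for T0 and status recovers part of that.
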